### Outcome measurements

#### Primary outcome

The primary outcome is the percentage change from baseline to the end of the study (after the 12-week intervention and after another 4-week follow-up) in LDL-C. The calculated LDL-C concentration will be determined at screening (entry to the study), day 1 (after TLC is completed and eligibility is determined), week 6, and week 12. LDL-C will be measured by preparative ultracentrifugation by the central laboratory. The LDL-C concentration calculated at screening will be reported only for the eligibility decision. The baseline lipid measurements for the purpose of analysis will be the day-1 lipid measurement after TLC (lipid stabilization). This will be collected after a ≥9-h fast and before receiving intervention.

#### Secondary outcomes

The secondary outcomes consist of three aspects: efficacy, safety and adherence. The efficacy outcomes include, from the baseline to the end of the study (after 12-week intervention and after another 4-week follow-up), the absolute change in LDL-C, the percentage change in HDL-C, the percentage change in total cholesterol (TC), the percentage change in TG, and the rate of subjects achieving LDL-C goal (see Table 5 in Appendix 1) [21]. The safety outcomes will be assessed by the physical examination, vital signs (including sitting blood pressure (BP) and heart rate (HR), electrocardiogram (ECG) and subject incidence of adverse events, after 12-week intervention and after another 4-week follow-up. The adherence outcome will be examined by the adherence rate, calculated as:$$ \mathrm{Adherence}\ \mathrm{Rate}=\mathrm{Number}\ \mathrm{of}\ \mathrm{treatments}\ \mathrm{conducted}/\mathrm{Number}\ \mathrm{of}\ \mathrm{treatments}\ \mathrm{planned}. $$

### Study procedures

The study consists of four periods: Screening, TLC, Intervention, and Follow-up period. For the purpose of this study, a week is defined as seven calendar days. A month is defined as 28 days.

#### Screening

Screening is conducted among subjects who meet the inclusion criteria to determine the eligibility of subjects to enter the study. In order to determine the eligibility for the study, they will enter the screening process by signing and dating the Informed Consent Form for this study.

The following data will be obtained and procedures performed during initial screening:Written informed consentMedical historyVital signs (see Appendix 2)Review for adverse events (serious adverse events (SAEs) and study-related AEs are collected during screening)Concomitant therapyPhysical examination12-lead ECG in triplicate using centralized ECG services equipmentBlood draw for fasting lipids, chemistry and serum pregnancy (women of childbearing potential only) by central laboratory (Appendix 2)

#### TLC period

Subjects who complete the screening successfully and who meet the inclusion/exclusion criteria will initiate therapeutic lifestyle change (TLC). The TLC adherence report form is made and sent to subjects to monitor their lifestyle change process. Re-assessment will be conducted after the TLC period.

#### Intervention period

##### Intervention day-1 visit

According to the re-assessment of fasting lipids after the TLC, a decision will be made on whether the lipid level has arrived at the target level and whether subjects should continue with the intervention. For those who have not reached the target lipid level, they will undertake randomization and receive first administration of the intervention and the date for that is considered to be day 1. For those who have reached the target lipid level after the TLC, they will be followed up for another 6 weeks and re-assessed for relative indexes in week 6.

##### Week 6 visit (±3 days)

Re-assessment on the study indicators of subjects will be conducted, including efficacy, safety, and adherence.

##### Week 12 end of study visit (±3 days)

Re-assessment on the study indicators of subjects will be conducted, including efficacy, safety, and adherence.

#### Follow-up period

A 4-week follow-up after treatment will be done in order to measure and monitor AEs and the effects of treatments at week 16. The study indicators of subjects will include efficacy and safety.

#### Trial flowchart

(Please refer to the supplementary document: Fig. 3. Trial flowchart)

**Fig. 3 Fig3:**
[figure not shown]
Trial flowchart. This figure provides an overview of participant flow in this trial

### Sample size

A significance level of 0.95 and a power of 0.80 will be allocated for the calculation of sample size. In accordance with a previous study [17], we could employ an effect size of 0.343 on absolute value change of LDL-C value, and a standard deviation of 0.7. In this case we estimate that the sample size for the acupuncture group and active control group should be approximately 65, respectively. The total sample size needed is 130.

In case of missing observation and patients lost, we assume that 90% of subjects will remain in the study. Thus, the sample size for two groups should be roughly 70 for each group.

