**Methods:**

The study a multicenter, open-label, randomized, stratified, active-controlled, noninferiority trial with two parallel groups. Subjects with hyperlipidemia will be stratified into different groups by risk levels of heart diseases. They then will be instructed to the Therapeutic Lifestyle Change (TLC) diet. Those who have not reached the target lipid level will be randomly assigned to the treatments of either acupuncture and moxibustion or simvastatin with a 1:1 allocation. One hundred and thirty subjects are aimed to be recruited. The duration of intervention for this study will be 12 weeks, followed by another 4 weeks for post-treatment assessment. The primary outcome is percentage change from baseline to the end of the study in low-density lipoprotein cholesterol (LDL-C). Other indicators in lipid change, safety and adherence will also be assessed secondarily. The repeated measures, linear mixed-effects model will be applied to the analysis.

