#### Primary objectives

To evaluate the effect of 12 weeks of acupuncture and moxibustion compared with active control, on percentage change from baseline in low-density lipoprotein cholesterol (LDL-C) among those with hyperlipidemia.

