### Statistical methods

#### Dataset analysis

For the primary endpoint of percentage change in LDL-C from baseline, the efficacy of acupuncture and moxibustion will be evaluated at week 12 by comparing the treatment effect to that of the active control group. A type I error of 0.05 will be allocated to the test.

There are three main analysis sets:Full analysis set (FAS): includes all randomized subjects who have received at least 1 investigational treatmentCompleter Analysis Set (CAS), includes subjects in the FAS who completed their scheduled intervention and have a nonmissing LDL-C value at week 12Effect Durability Analysis Set (EDAS), includes subjects in the FAS who completed their scheduled intervention and have non-missing LDL-C values at week 6 and week 12

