#### Statistical analysis plan

The primary analysis set for the primary endpoint is the FAS. It is to use the repeated measures, linear mixed-effects model, including terms for treatment group, stratification factor, baseline LDL-C, scheduled visit and the interaction of treatment with scheduled visit. Missing values will not be imputed when the repeated measures, linear mixed-effects model is used.

We will use the chi-squared test for binary outcomes, and the *t* test for continuous outcomes. For subgroup analyses, we will use regression methods with appropriate interaction terms (respective subgroup treatment group). Multivariable analyses will be based on logistic regression for binary outcomes and linear regression for continuous outcomes. We will examine the residual to assess model assumptions and goodness-of-fit. For timed endpoints, such as mortality, we will use the Kaplan-Meier survival analysis followed by the multivariable Cox proportional hazards model for adjusting for baseline variables. We will calculate Relative Risk (RR) and RR Reductions (RRR) with corresponding 95% confidence intervals to compare dichotomous variables, and difference in means will be used for additional analysis of continuous variables. *P* values will be reported to four decimal places with *P* values < 0.05 reported as *P* < 0.05. Up-to-date versions of R (R Foundation) will be used to conduct analyses. For all tests, we will use two-sided *P* values with alpha no greater than 0.05 level of significance. We will use the Bonferroni method to appropriately adjust the overall level of significance for multiple primary outcomes, and secondary outcomes.

In investigation of the robustness of the analysis results, the primary analysis will be repeated using the CAS. In addition, parametric analysis of covariance (ANCOVA) and appropriate nonparametric methods will be used on the FAS, in which missing data will be imputed using the last-observation-carried-forward (LOCF) approach. The primary analysis will also be repeated for subgroups of interest.

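### The recruitment target of 130 omits the plan's own 10% loss allowance and contradicts its 140, and the 80% power is calculated for absolute LDL-C change, not the primary percentage change

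*Protocol article*

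**What the plan says.** The Sample size section of the protocol article opens with "A significance level of 0.95 and a power of 0.80 will be allocated for the calculation of sample size". Citing a previous study, it continues: "we could employ an effect size of 0.343 on absolute value change of LDL-C value, and a standard deviation of 0.7". From these it obtains about 65 per group, 130 in total. It then allows for missing observations and losses by assuming 90% retention, and ends with "Thus, the sample size for two groups should be roughly 70 for each group", which is 140 in total.

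Two other places give the number to recruit. The abstract (Methods) says "One hundred and thirty subjects are aimed to be recruited", and the Trial status section lists a target of 130.

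The primary objective is the effect "on percentage change from baseline in low-density lipoprotein cholesterol (LDL-C) among those with hyperlipidemia". The Primary outcome and Dataset analysis sections use the same percentage scale. The Secondary objectives and Secondary outcomes sections list absolute change in LDL-C as secondary.

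On the error rate, Dataset analysis says "A type I error of 0.05 will be allocated to the test" and the Statistical analysis plan section says "For all tests, we will use two-sided *P* values with alpha no greater than 0.05 level of significance".

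**The concern.** The number given as the recruitment target is the number the plan needs after losses. The Sample size section recognises that more must be randomized, but the larger number reaches neither the abstract nor the trial status entry. A team that stops at 130 would believe it has 80% power when the plan's own retention assumption says otherwise.

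Two further points concern the same section. The step from 65 to 70 is not what 90% retention gives. And the difference and SD are on the absolute scale, so the stated power belongs to a secondary outcome. The plan gives no difference, margin or SD in percentage points.

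In a noninferiority trial, low power mainly raises the chance of an inconclusive result. It does not by itself produce a false claim of noninferiority.

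**Working it through.** **Inputs.** Difference 0.343, SD 0.7, power 0.80 and 90% retention (Sample size); two-sided alpha 0.05 (Dataset analysis; Statistical analysis plan); 1:1 allocation (Trial design). No unit is given for 0.343, and it is not labelled as a noninferiority margin.

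**Reproducing the plan's figure.** Per group,

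n = 2 × (1.960 + 0.842)² × (0.7/0.343)² = 2 × 7.851 × 4.165 = 65.4.

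This agrees with the stated figure of approximately 65 (66 if rounded up). Treating 0.343 as a noninferiority margin with a true difference of zero and one-sided alpha 0.025 gives the same result. Other readings do not fit: one-sided alpha 0.05 gives 52 per group, and 0.343 as a standardised effect gives 134. So 65 rests on two-sided 0.05 (equivalently one-sided 0.025).

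**Loss allowance.** 65/0.9 = 72.2, so 73 per group, 146 in total. The shortcut 65 × 1.1 = 71.5, so 72, does not give 70 either.

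**Power after 10% loss.** With n evaluable per group, power ≈ Φ(0.49 × √(n/2) − 1.960), where 0.49 = 0.343/0.7.

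| Randomized | Evaluable per group | Power (normal) | Power (t-based) |
|---|---|---|---|
| 130, no loss | 65 | 79.8% | 79.2% |
| 130 | 130 × 0.9/2 = 58.5 | 75.5% | 74.8% |
| 140 | 70 × 0.9 = 63 | 78.5% | 77.9% |
| 146 | 73 × 0.9 = 65.7 | 80.2% | 79.6% |

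For 58.5 per group: 0.49 × √29.25 − 1.960 = 0.690, and Φ(0.690) = 0.755.

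**Primary scale.** The same formula for percentage change needs a difference (or margin) and an SD in percentage points. The protocol gives neither, so power for the primary outcome cannot be computed from it.

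**The case against.** **The planned analysis may recover the loss.** The primary analysis is a repeated-measures mixed model on the full analysis set, adjusted for baseline LDL-C and the stratification factor. It can use week 6 data from subjects who miss week 12. On the absolute scale, 58.5 per group would regain 80% if adjustment removed about 1 − 58.5/65.4 = 10.5% of the variance; 63 per group would need about 1 − 63/65.4 = 3.7%. This is a fair qualification, and 75.5% should be read as a simple two-sample figure. But the Sample size section claims no such gain, and the protocol gives no correlation from which to estimate one.

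**The figure of 70 is only approximate.** The text says roughly 70, and 140 randomized still leaves about 78.5%. This stands: on its own, that step is coarse rounding worth about 1.5 points. The material contradiction is 130 against 140.

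**Significance level of 0.95.** A reader might infer that the calculation used a wrong alpha. It did not. The two analysis sections state 0.05 two-sided, and 65 reproduces with that value. It is a confidence level misnamed, and no number changes.

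**Absolute against percentage change.** A reader might infer that the mismatch shows power below 80% for the primary outcome, or that the calculation must fail because entry LDL-C thresholds run from 100 to 160 mg/dL across risk groups. The documents support neither. Dividing both 0.343 and 0.7 by any one baseline leaves their ratio at 0.49, and n depends only on that ratio, so such a conversion does not change n. The real percentage-scale SD and margin are not given, so power there may be higher or lower than 80%.

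**Conclusion.** The point holds in three parts of unequal weight.

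- **Wrong as written:** the target of 130 contradicts the loss-adjusted 140. With the plan's own 10% loss it gives about 75.5% power, roughly 4.5 points below the stated 80%.
- **Small arithmetic slip:** 90% retention requires 73 per group (146), not 70. At 140 the shortfall is about 1.5 points.
- **Unsupported:** the 80% is calculated for a secondary outcome. Nothing in the protocol establishes power for percentage change in LDL-C, in either direction.

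The power figures assume a two-group comparison of means on the absolute scale, two-sided alpha 0.05, equal 10% loss in both groups, and no gain from baseline adjustment or partial data.

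**What to change.** 1. Give one recruitment target in the abstract, the Sample size section and the Trial status section, with the power it delivers after 10% loss on the current inputs: 130, about 75%; 140, about 78.5%; 146, about 80%. Any of these is acceptable if stated plainly. More patients are needed only if the sponsor wants to keep 80%.
2. Redo the calculation for percentage change in LDL-C at week 12, with the difference or noninferiority margin and the SD in percentage points and their source. If credit is taken for baseline adjustment, state the assumed correlation. This recalculation may replace the numbers in item 1.
3. Replace the significance level of 0.95 with two-sided alpha 0.05 (one-sided 0.025 for the noninferiority comparison).

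The cost is one recalculation, edits in three places and possibly a less favourable power statement.

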### Stratified and blocked randomization

According to the re-assessment of fasting lipid after the TLC, a decision will be made on whether the lipid level has arrived at the target level and whether subjects should continue with the intervention. Subjects will receive the intervention at the site at which they are recruited. Within each site, subjects will be stratified by risk groups (0–1 risk group, 2+ Risk Factor Group, and CHD or CHD risk equivalents group), as target lipid levels differ according to different risk groups. Subjects who have not reached the target lipid level after TLC, will be randomized to two arms at a ratio of 1:1 (acupuncture and moxibustion versus simvastatin). The randomization will be blocked (size = 4) to ensure that equal numbers of subjects are allocated to each arm. A computer-generated, blocked randomization sequence will be used to randomize subjects in the study. Assignment to the two treatment arms will be generated by the principal biostatistician using R (version 3.1.1; R Foundation for Statistical Computing, Austria. ISBN 3-900051-07-0) before the start of the study. The sequence will be held in a secure location in the hospital by the principal biostatistician; the researchers will be blinded to the number of cases in each randomization block and individual subject allocation will be conducted remotely via telephone based on the randomization sequence. Once a subject is eligible to receive the intervention, the principal biostatistician will be informed and will let physicians know each subject’s allocation by phone.

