### Study setting

The study will include four sites in Hunan, China. They are First Affiliated Hospital of Hunan University of Chinese Medicine, Changsha Chinese Medicine Hospital, Yueyang Chinese Medicine Hospital, and Chenzhou Chinese Medicine Hospital. Other sites may be added for participation in the study. Sites that do not enroll any subjects within 3 months of site initiation will be closed. Each site must follow this study protocol; otherwise, it will be closed. The Steering Committee will audit and review the intervention performed in each site, to ensure that they are following this protocol.

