### Blinding

Due to the nature of the acupuncture and moxibustion interventions, neither participants nor care providers can be blinded to allocation and treatment stages, but are strongly inculcated not to disclose the allocation status of the participant at the follow-up assessments. The outcome assessment will be conducted by outcome assessors blind to the treatment allocation. In the stage of data analyses, an employee outside the research team will feed data into the computer in separate datasheets so that the data analysts can analyze the data without having access to information about the allocation.

To maintain the overall quality and legitimacy of the clinical trial, code breaks should occur only in exceptional circumstances when knowledge of the actual treatment is absolutely essential for further management of the patient. Investigators, including the outcome assessors and data analysts blind to treatment allocation, are encouraged to discuss with the medical advisor physicians if they believe that unblinding is necessary. The investigator is encouraged to maintain the blind as far as possible. The actual allocation must *not* be disclosed to the patient and/or other study personnel. There should not be any written or verbal disclosure of the code in any of the corresponding patient documents. The investigator must report all code breaks (with reason) as they occur on the corresponding Case Report Form page. Unblinding should not necessarily be a reason for study drug discontinuation.

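### The protocol prints the fixed block size of 4 that it says researchers will not know, so a site tracking its own open-label allocations could probably deduce about 30% of assignments in advance

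*Protocol article*

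**What the plan says.** The Protocol article, section Stratified and blocked randomization, sets out these elements:

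- Ratio: subjects still above target after the diet phase "will be randomized to two arms at a ratio of 1:1 (acupuncture and moxibustion versus simvastatin").
- Strata: "Within each site, subjects will be stratified by risk groups (0–1 risk group, 2+ Risk Factor Group, and CHD or CHD risk equivalents group").
- Blocks: "The randomization will be blocked (size = 4) to ensure that equal numbers of subjects are allocated to each arm". No other size is mentioned.
- Release: "individual subject allocation will be conducted remotely via telephone based on the randomization sequence", from a list that the principal biostatistician keeps. After eligibility is confirmed, the biostatistician "will let physicians know each subject’s allocation by phone".
- Concealment of block size: the section also claims that "the researchers will be blinded to the number of cases in each randomization block".

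The same section says that subjects are treated at the site that recruited them, and that the list is generated before the study starts. Study setting adds "The study will include four sites in Hunan, China", with the option of more. Blinding states that "neither participants nor care providers can be blinded to allocation and treatment stages". Trial status gives first enrolment as December 2014 and the status as recruiting.

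**The concern.** Keeping the block size from researchers is a useful safeguard only if they cannot find it out. Here it is printed in the public protocol, one clause away from the statement that it is hidden. The other conditions for deduction are also in the text: a single size, a 1:1 ratio, stratification within site, treatment at the recruiting site, physicians told every allocation, and no blinding of care providers. Remote telephone release keeps the list out of sight, but it does not stop a site from counting its own past assignments.

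At stake is selection at enrolment. Someone who can foresee the next arm can hasten, delay or discourage a particular patient's entry. The primary model under Statistical analysis plan contains treatment, stratification factor, baseline LDL-C, visit and treatment by visit. It can absorb selection that works through baseline LDL-C or risk group, but not selection on traits outside the model, such as expected adherence. In a noninferiority comparison, selection that favours acupuncture and moxibustion would push towards a false claim of noninferiority.

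**Working it through.** The protocol gives no predictability figure to reproduce, so the check starts from its design inputs.

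**Inputs.** Block size 4 and ratio 1:1 (Stratified and blocked randomization); 4 sites × 3 risk groups = 12 strata (Study setting; Stratified and blocked randomization); N = 130, or 2 × 70 = 140 with the allowance for loss (Sample size).

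**Step 1: one complete block of 4.** There are 6 equally likely orders of two A and two B. The next arm is certain once one arm has both its places filled.

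| Position | P(next arm certain) | P(best guess right) |
|---|---|---|
| 1 | 0 | 1/2 |
| 2 | 0 | 2/3 |
| 3 | 1/3 | 2/3 |
| 4 | 1 | 1 |

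At position 3, the first two match with probability 1/3. The arm is then certain; otherwise the guess is even. So the best guess is right with probability 1/3 + (2/3)(1/2) = 2/3.

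- Share certain: (0 + 0 + 1/3 + 1)/4 = 1/3 = 33.3%.
- Best guess right: (1/2 + 2/3 + 2/3 + 1)/4 = 17/24 = 70.8%, against 50% by chance.

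**Step 2: unfinished last blocks.** If every block were completed, the count would be 130/3 = 43.3 or 140/3 = 46.7. A last block holding r subjects falls short of r/3 certain allocations by 0, 1/3, 2/3 or 2/3 for r = 0, 1, 2, 3. If the four values are about equally likely, the mean shortfall is (0 + 1/3 + 2/3 + 2/3)/4 = 5/12 per stratum, or 12 × 5/12 = 5 over 12 strata.

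- N = 130: 43.3 − 5 = 38.3, or 29.5%.
- N = 140: 46.7 − 5 = 41.7, or 29.8%.

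A simulation that spreads subjects at random over 12 equally likely strata gives the same figures. An assumed unequal spread over sites and risk groups changes them by less than 0.1 percentage point.

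**Step 3: if blocks ran by site only.** Four lists give a shortfall of 4 × 5/12 = 1.7, so 41.7 of 130 (32.1%) or 45.0 of 140 (32.1%).

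**Step 4: randomly varying sizes.** Simulated strata of 12 subjects, with an observer who knows the set of possible sizes but not which was drawn:

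| Sizes | Certain | Best guess right |
|---|---|---|
| 4 only | 33% | 70.8% |
| 4 or 6 | about 6% | about 68% |
| 2, 4 or 6 | about 3% | about 69% |
| 4, 6 or 8 | about 2% | about 66.5% |

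Varying the size removes most of the certainty, but only about 2 to 4 points of best-guess success.

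**The case against.** **Blocking within strata is inferred.** The text says that subjects are stratified within each site, but then speaks of a randomization sequence in the singular. If one central list served all four sites, a site seeing only its own patients could rarely deduce the next arm. This stands as a condition on the figures. The section heading and the within-site sentence make stratified blocks the likelier reading, and blocking by site alone would give a slightly higher share.

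**The list itself is protected.** Allocation is released by telephone only after eligibility is confirmed. That is true, and it prevents anyone reading ahead on the list; it does not prevent deduction from a known block size.

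**There is limited room to steer.** Eligibility rests on central-laboratory LDL-C thresholds and on missing a fixed goal after the diet phase. The endpoint is a central-laboratory value, with assessors blind to allocation. This narrows the risk, but it leaves open the timing and encouragement of entry. Blinded assessment protects measurement, not enrolment.

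**Baseline adjustment helps.** A reader might infer that the resulting bias cannot be adjusted away at all. That goes too far, because the primary model includes baseline LDL-C and the stratification factor. What stays uncorrected is selection on traits outside the model.

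**The remedy is partial.** Steering needs only better-than-chance guessing, and best-guess success barely moves with varying sizes. This is correct, and the benefit should be described in those terms.

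**Conclusion.** The concern holds in a limited form. The protocol's statement that block size is concealed is contradicted by the size it prints, and the open-label, site-based conduct lets a site make use of it. The size is about 30% of assignments deducible in advance: roughly 38 of 130 or 42 of 140 subjects. In complete blocks the figures are 33.3% certain and 70.8% best-guess success.

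These figures assume blocks within site-by-risk strata, 12 equally likely strata, and staff who track their own stratum's allocations. Added sites would mean more unfinished blocks and a somewhat lower share.

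A reader might go further and infer that sites do know these allocations, or that the trial's result is already biased. The documents do not support that. They show a capability, no site is shown to have used it, and no bias in LDL-C units can be derived from them. The weakness should be corrected while allocations remain, but it does not by itself invalidate the trial.

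**What to change.** For allocations not yet used:

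1. Regenerate the within-stratum lists with randomly varying block sizes, and hold the sizes in a restricted document.
2. In the protocol, replace the stated size of 4 with wording such as *randomly varying block sizes, not disclosed to sites*.
3. State explicitly that blocks run within site-by-risk strata.

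The ratio, the strata and the telephone procedure stay as they are.

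The cost is a short re-run in R and a brief amendment. Possible imbalance per stratum becomes slightly larger. Because the list was generated before the start and the trial is recruiting, the change also needs documented version control and a rule for partly filled blocks in up to 12 strata. The documents do not say how many allocations remain. If none do, what is left is to report the predictability openly and to examine baseline balance between the arms.
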